## 4.5 Participant Withdrawal

Participants may voluntarily withdraw from the study at any time. If a participant chooses to withdraw during an assessment period they can choose not to have their assessment responses submitted to the study team.

Participants also may be withdrawn if the principal investigator, study sponsor, government or regulatory authorities, or site institutional review boards (IRBs) terminate the study prior to its planned end date. In such cases the Principal Investigator will review the reasons for withdrawal with the IRB and Protocol Biostatistician prior to participant notification. The Principal Investigator may decide to include data collected prior to participant withdrawal in study analyses.

Every reasonable effort will be made to complete a final assessment of participants who leave the study prior to the planned termination date. Study staff will record the reason(s) for all withdrawals from the study in participants’ study records.

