## 6.5 Follow-up Behavioral Assessments

At 12 months and 30 months a follow-up behavioral assessment will be conducted among eligible and consenting participants in order to assess outcome and mediating variables. We will use the same procedures described for the baseline assessment.

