## 6.6 Follow-up STI Assessment

At 30 months urine and blood specimens will be collected from 100% of eligible and consenting men for STI testing (NG, TV, CT) and HIV.

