**Behavioral Survey**

An approximately 1 hour behavioral survey instrument will be created and formatted in Samsung Galaxy tablets. The survey will be comprised of variables that assess, but are not limited to, demographic data, HIV risk and protective behaviors, social and sexual networks, gender-based violence perpetration and victimization, hope, collective efficacy, emotional distress, social support, alcohol and drug use, and work and expenditures. The behavioral survey form will be used at baseline, and 12 and 30 month follow-ups.

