**Aim 2**

HIV risk, gender-based violence perpetration, and their mediators will be assessed at baseline, 12 and 30 months. STI prevalence assessments will occur at baseline and 30 months. Participants selected to provide a biological specimen must have completed the behavioral assessment to be eligible. Separate written consent will be necessary for the behavioral and biological assessments. Potential participants will be excluded from participation based on an inability to provide informed consent. All consent documents will be stored in locked cabinets. Copies of the informed consent script will be provided to prospective participants to keep.

Research assistants will begin each interview by confirming the eligibility of participants. All eligible participants will then be read the informed consent script in Kiswahili and given the chance to ask questions or clarifications on what they are being asked to do in the study. Participants will acknowledge their consent by initialing the line for behavioral assessment and writing the date and their signature on the form.

Upon completion of the survey, participants selected for the biological assessment will meet with nurses who will administer the biological consent. Nurses will explain the purpose and procedure for blood and urine collection in private. Participants will acknowledge their consent by initialing the line for biological assessment.

Participants not selected for the biological assessment will have the opportunity to receive a symptomatic STI assessment with nurses. Nurses will explain the procedure for symptomatic STI assessment. Participants will acknowledge their consent by initialing the line for symptomatic STI assessment.

Written informed consent will be obtained from each participant in the qualitative sub-studies, prior to their participation. Participants will be provided with a copy of their consent form.

The host site has prior experience in obtaining informed consent for prevention trials within the cultural context. The informed consent procedure for this study has been designed to maximize understanding of potential risks. Consent forms will be translated into Kiswahili and piloted with 50 participants to ensure the script is understandable.

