| Q007 | How often would you say you come to camp X? | EVERY DAY  SEVERAL TIMES A WEEK  ONE TIME PER WEEK  COUPLE TIMES A MONTH  ONE TIME PER MONTH  LESS THAN ONCE A MONTH | 1  2  3  4  5  6 | **END**  **END**  **END** | ELIG7 |
| Q008 | Are you a member of any other camps? | NO  YES | 0  1 | **Q012** | ELIG8 |
| Q009 | What are the names of these other camps?  *Note: If participant is a member of more than 2 other camps, separate these camp names with a comma.* |  |  |  | ELIG9 |
| Q010 | [DO NOT READ OUTLOUD]  By looking at the list of 60 study camps, determine whether participant is a member of another study camp. Is the participant a member of another study camp? | NO  YES | 0  1 | **Q012** | ELIG10 |
| Q011 | I see that you are also a member of camp X. Which of these camps would you consider to be your PRIMARY CAMP? By primary camp, I mean you spend more time in this camp than any other camp. | This Camp  Other Camp |  | **END** | ELIG11 |
| Q012 | Have you answered these types of questions and have you previously provided a sample of your blood and urine to our study staff? | NO  YES | 0  1 | **END** | ELIG12 |
| Q013 | Do you plan to live in Dar es Salaam for the next 30 months? | NO  YES | 0  1 | **END** | ELIG13 |
| Q014 | Are you willing to provide a phone number and contact information for two family members or close friends so that study staff can contact you in the future? | NO  YES | 0  1 | **END** | ELIG14 |

*Interviewer:*

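### The protocol contradicts itself on whether eligibility is re-applied at 12 and 30 months; read literally, men could be excluded after randomisation from both primary endpoints

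*Protocol*

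**What the plan says.** **Text that re-applies eligibility.** Section 10.2 (Aim 2) begins by listing the baseline, 12-month and 30-month assessments, then states: "Research assistants will begin each interview by confirming the eligibility of participants". Section 6.1 says that each survey round covers the eligible members of the selected camps. Section 6.5 says that at 12 and 30 months "a follow-up behavioral assessment will be conducted among eligible and consenting participants", and adds: "We will use the same procedures described for the baseline assessment". Section 6.6 says that at 30 months "urine and blood specimens will be collected from 100% of eligible and consenting men". Section 8.2.3 says of the instrument: "The behavioral survey form will be used at baseline, and 12 and 30 month follow-ups".

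**What eligible means.** The term is defined only in section 4.3.1 (including weekly camp visits and intent to live in Dar es Salaam for 30 months) and in the Section 0 screener of Appendix D. Section 0 ends the interview on low camp attendance (Q007), on naming another study camp as primary (Q011), on an earlier interview and sample (Q012) and on residence plans (Q013).

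**Text that fixes eligibility at baseline.** Section 4.3.2 ties exclusion to the baseline behavioral assessment. Section 3.3 has all participants surveyed at the three time points and all men tested at endline, with no eligibility condition. Sections 4.4 and 4.5 trace men who miss visits and seek a final assessment from those who leave early.

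**Withdrawn men.** Sections 4.5 and 10.7 both say: "The Principal Investigator may decide to include data collected prior to participant withdrawal in study analyses".

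**The concern.** At enrolment these criteria define the cohort and do no harm. At 12 and 30 months, weekly attendance, primary camp and plans to stay are all events after randomisation. Attendance in particular may respond to the intervention: loan groups are formed within a camp, each camp is a repayment centre, and centres meet weekly (5.2.2). Filtering outcome collection on such a variable leaves arms that are no longer comparable, for a reason that the intervention itself may have produced.

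Both primary endpoints would be reached. Violence perpetration comes from the survey, and section 10.2 requires a completed survey before a specimen is taken, so a man stopped at a screener would also miss his endline STI test.

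A later analysis plan could not repair this, because the outcomes would never have been collected. The withdrawal clause raises a smaller, related problem: whether some men's data count is left to judgement in a trial whose allocation is drawn at a Community Advisory Board meeting and reported to that board (4.2, 12.1).

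**Working it through.** The point contests no stated figure, so the main check is to set the texts against each other.

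| Question | Points to re-screening | Points to baseline only |
|---|---|---|
| Who is surveyed at 12 and 30 months? | 6.1, 6.5: eligible men | 3.3: all participants |
| Who has the 30-month STI test? | 6.6: eligible men | 3.3: all men |
| When is eligibility checked? | 10.2: at each interview | 4.3.2: exclusion from the baseline assessment |
| Which form is used? | 6.5, 8.2.3: same procedures, same survey form | 6.3 cites Appendix D for baseline; 7.4.1, 7.6.1 and 7.6.3 add follow-up items that Appendix D lacks |

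No section says that Section 0 is re-applied at follow-up, and none says that it is not.

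**Would the missing-data provisions catch it?** Section 4.4 counts a man as lost when five contact attempts fail. A man stopped at a screener has been contacted, so he is not lost by that definition. Section 9.1.5 examines missingness due to loss to follow-up. Section 9.1.3 weights by the inverse of response rates, without saying whether men found ineligible stay in the denominator. Such men could therefore fall outside both provisions.

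**Possible loss.** Inputs: 1249 men (Protocol Summary; section 3.2.3 gives 1252); 20% attrition (9.1.1, stated there for a different planning sample); share stopped at follow-up, an assumed 10% to 30%, since the protocol gives no rate.

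- After attrition: 1249 × 0.80 = 999.
- 10% stopped: 999 × 0.90 = 899.
- 30% stopped: 999 × 0.70 = 699.

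**How an effect could appear where there is none.** Every input here is assumed. In both arms 75% of men would attend weekly regardless and have 30% violence. The other 25% would stop attending in the control arm.

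- Case A: these men have 15% violence, and the intervention keeps 15 of the 25 points attending. The true rate in each arm is 0.75 × 0.30 + 0.25 × 0.15 = 0.2625. Observed, control: 0.30. Observed, intervention: (0.75 × 0.30 + 0.15 × 0.15) / 0.90 = 0.275. Odds ratio: (0.275/0.725) / (0.30/0.70) = 0.885.
- Case B: these men have 10% violence, and 20 points are kept. Observed, intervention: (0.75 × 0.30 + 0.20 × 0.10) / 0.95 = 0.258. Odds ratio against 0.30: 0.811.

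If men who stop attending were more violent than those who stay, the bias would run the other way. The cases show the mechanism. They do not predict its size or direction.

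**The case against.** The strongest reply is that Section 0 is simply an enrolment screener. The sentence in 10.2 names no screener, sits beside text on prospective participants, and is followed by paragraphs separating men selected for biological testing from men not selected, which fits baseline but not 30 months. Appendix D opens with a recruitment script, and its age check is fixed to a 1998 birth year. The withdrawal grounds in 4.5 and 10.7 do not name lapsed attendance or plans to move. All of this stands, and it makes baseline-only screening a plausible intent. It does not remove the instructions in 6.1, 6.5, 6.6 and 10.2.

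A reader might infer more than the protocol supports:

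- **That half the cohort would be removed by Q012**, which asks "Have you answered these types of questions and have you previously provided a sample of your blood and urine to our study staff". Half of 1249 is 624.5; if only sexually active men were sampled (6.4), the planning ratio in 9.1.1 gives 624.5 × 36.2/52, or about 435. Neither is a forecast. Q012 follows questions on membership of several camps and reads as a check against double enrolment, and using it at 30 months would defeat the plan in 3.3 to test all men. The answer that triggers its stop is also not legible in the table.
- **That loan meetings in camp directly raise attendance.** Section 5.2.2 organises repayment by camp but does not say where centres meet. An effect on attendance is plausible, not documented.
- **That all withdrawn men's data are discretionary.** In 4.5 the sentence follows early termination of the study; in 10.7 it follows withdrawal by the investigator. A man who withdraws during an assessment may himself withhold those responses. The discretion covers some withdrawn men, not all.

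**Conclusion.** The point holds as a contradiction in the protocol's rules for who is followed up. Sections 6.1, 6.5, 6.6 and 10.2, with the definitions in 4.3.1 and Appendix D, allow exclusion after randomisation on attendance, primary camp or residence plans; sections 3.3 and 4.3.2 say otherwise; nothing settles it. If the literal reading were followed, both primary endpoints would be affected and the comparison by randomised arm would be open to selection bias.

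It would go too far to conclude that men will be dropped or that intention-to-treat is already broken, because re-use of the screener is inferred from several sections and stated in none. The size is unknown: the 899 to 699 range and the odds ratios of 0.885 and 0.811 rest on assumed inputs. It still needs correcting in the protocol before follow-up, since uncollected outcomes cannot be recovered. The discretion over some withdrawn men's data is a separate, smaller defect that the same edit can close.

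**What to change.** 1. State in 4.3 and 10.2 that the 4.3.1 criteria and Section 0 of Appendix D are applied once, at baseline, and leave Section 0, including Q012, out of the follow-up form.
2. In 6.1, 6.5 and 6.6, replace the reference to eligible men, for follow-up rounds, by all men enrolled at baseline who consent. State that they are followed and analysed in the arm of their baseline camp, whatever their current attendance, camp or plans.
3. Record current camp attendance at follow-up as a variable and do not use it as a filter.
4. In 4.5 and 10.7, replace the investigator's discretion by one rule: data collected before withdrawal are included for everyone unless the participant withdraws permission.

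The cost is a few sentences of protocol text, a small edit to the follow-up form on the tablets, and some extra tracing of men who have left their camp, for which 4.4 already provides the means.

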## 10.3 Confidentiality

### 10.3.1 Local Protections

Confidentiality of all study participants will be strictly maintained across all study components. All field staff who have not completed research ethics training will attend the one-day FHI 360 Research Ethics Training Curriculum for Community Representatives conducted by trained staff during the Training of the Trainers Meeting at the start of the project. A major component of the training involves a presentation and discussion of the principles of research ethics, with emphasis given to confidentiality. Field staff must pass the FHI 360 Research Ethics Training Curriculum for Community Representatives post-test to participate in data collection with participants. <http://www.fhi.org/en/RH/Training/trainmat/ethicscurr/retccr.htm>.

Staff conducting interviews for Aim 1 will select private areas at camps to ensure participant confidentiality. Upon arriving at camps, interviewers will scan the camp landscape to find the appropriate location for interview location. In the case that no such place exists, the interviewer will consult with camp leaders to arrange private areas for interviews to maintain confidentiality.

During the baseline behavioral assessment participants will be asked to provide written consent to participate in the intervention. Participants will be informed that they will be re-contacted to participate in follow-up behavioral assessments and may be selected for STI testing. Upon providing written consent to participate in the study, the participant will provide contact information. For the study components in which participants are required to provide written informed consent, all study data, laboratory specimens, reports, and study data collection, process, and administrative forms will be identified by a coded number only, to maintain participant confidentiality. All study data will be stored separately from study records that contain names or other personal identifiers (such as informed consent forms or locator forms). For post-test support services no identifying information will be linked to the participant's STI test results.

Forms, lists, logbooks, appointment books, and any other listings that link participant ID numbers to other identifying information must be stored in a separate, locked file in an area with limited access at the study site headquarters. Participant names and corresponding participant IDs entered into a computer database must be password protected and must be maintained in a directory separate from any study-specific data. File encryption is encouraged, but not required when stored on a password protected device.

For participants who provided written informed consent, study-related information will not be released without the written permission of participants.

### 10.3.2 Statistical and Data Management Protections

Access to all study databases housed with the Data Manager in Delhi, India and UNC will be password protected to ensure confidentiality of study participants. Any copies of data query forms, utilization logs, and all adverse event reports will be stored in locked file cabinets. Only study PIs and the data research coordinator will have access to secure documents. Any breach in confidentiality protocol will immediately be written up as an adverse event, and submitted to the IRB. The data to be analyzed at UNC only include anonymous study IDs with no other information identifying the subjects. The databases are stored electronically on university computers protected by a firewall and allow only local access using a password.

## 10.4 Benefits

**10.4.1 Individual Benefits**

- All study participants will have the opportunity to either learn their status on a number of STIs (NG, CT, TV) or receive symptomatic assessments of STIs. Participants who test positive for any STI will be provided with treatment free of charge and access to a trained psychologist as needed. Participants exhibiting STI symptoms will be referred to clinics that provide free treatment.
- Participants may benefit from knowing that the information learned from this study will help to improve the situation of youth like themselves.
- Participants may also benefit from talking with the trained peer leaders about social concerns that they face.

### 10.4.2 Community Benefits

- This trial tests the efficacy of a combined microfinance and HIV prevention trial in reducing HIV and gender-based violence perpetration by men in a country with high HIV prevalence, which if successful, could be disseminated more broadly in urban Tanzanian camps. This study is designed to answer an important scientific question about the ability of a community-based, behavioral HIV intervention to reduce the incidence of HIV in high-prevalence area (an estimated 2.7% of females and 1.2% of males aged 15-24 years are HIV-infected in Tanzania) ([TACAIDS & NBS OCGS, 2013](#_ENREF_93)). The outcome of this study could have a significant public health impact in communities and countries around the world.
- The population of focus in this study is young, urban men. Identifying venues to access male social networks, especially in urban settings where HIV prevalence is often highest and men are not being reached, is a challenge. Camps, the intervention unit in this study, provide potential venues to access social networks of men.

### 10.4.3 Benefits to Humanity

If the trial is successful there are potentially enormous social benefits that can be gained from the study.  We expect this intervention to be effective, cost-effective, sustainable and easily disseminated in other developing country settings.  Youth in sub-Saharan Africa and elsewhere continue to be disproportionately affected by the HIV epidemic, and there are limited strategies that have proven effective at reaching youth.  If proven efficacious, we feel this multi-level approach to reaching young men at risk for HIV transmission and acquisition will have widespread application in other settings.

## 10.5 Risks

### 10.5.1 Individual Psychosocial Risks

We believe the risk of participants experiencing negative psychological events as a result of participation in the study will be infrequent.    It is possible that some participants may experience these outcomes as a result of responding to the survey questions or participation in the health promotion component of the intervention trial.   We will train our interviewers in techniques of interviewing to help minimize the embarrassment and emotional distress that men may feel responding to personal questions about their relationships.  Health leaders from camps will also be trained in techniques to help minimize the embarrassment that men may feel as a result of participating in the health promotion component of the study.  It is also possible that men may experience some social or psychological risks if they learn they are positive for a sexually transmitted infection.  Nurses who will take the specimens and provide the results to the men will be trained in appropriate counseling procedures to communicate and discuss results with the men.  If men have social or psychological concerns beyond what nurses feel they are capable of responding to the nurses will be trained to refer these men to the site PI, [name], who is a trained psychologist with experience working with adolescents.

### 10.5.2 Individual Physical/Health Risks

We believe that the specific research components in this study will not subject participants to any physical or health risks. Since the intervention includes a microfinance component there is the possibility that participants will experience financial gain. The possibility exists that participants with financial gain could be targeted for robbery, and thus potentially harmed physically. We believe this risk to be unlikely and had no such occurrences of robbery or mugging during a pilot study we conducted with a microfinance component. There is also the possibility that individuals taking a microfinance loan may not have successful businesses and become indebted. To minimize this risk numerous safeguards are in place to promote successful repayment (must attend business training, must have loan approved by group and camp leader, must deposit minimal savings), as well as booster sessions to help address business challenges. Taking a loan is voluntary and does not disclude individuals from further participation in the study. Nurses collecting blood samples with hypodermic needles may face occupational exposure to HIV and other STIs through accidental needle sticks. All nurses employed for this study are trained in proper precautionary procedures to prevent these accidents, and have been informed of post-exposure procedures to prevent infection.

### 10.5.3 Community Risks

Through participation in the study, camps may experience stigma, misperceptions, and/or negative rumors. For example, participating camps may be viewed as having a high prevalence of HIV as the reason for its inclusion in the study. These camps may also be perceived to be receiving special benefits beyond those outlined above; it may be perceived as receiving favored treatment. All these may lead to ostracism of and discrimination toward these camps and its members by neighboring communities.

